### Outcomes

#### Primary outcome

Intention to use condoms during vaginal sex with casual sexual partners over the next two months.

#### Secondary outcomes

Use of condoms during vaginal sex with casual sexual partners over two months post delivery.

Perceived likelihood of chlamydia.

Perceived severity of chlamydia.

Response efficacy for condom use.

Self-efficacy for using condoms during vaginal sex with casual sexual partners over the next two months.

### Statistical analysis

Prior to analysis, school codes will be removed from the data set by an independent researcher and intervention condition coded as A or B. This will blind analysts to intervention condition. Intention to treat analysis will be used so that data is used regardless of whether pupils are present or absent during the STI and chlamydia lessons in either of the intervention arms, and means are imputed for pupils with missing post-delivery and/or follow-up data. Whole classes or schools who drop-out during the study and don’t provide at least post-delivery data will be removed from the analysis.

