### Randomisation and allocation concealment

To avoid contamination, we will use cluster randomisation using schools as the randomisation unit. Schools will be allocated to either arm of the study using block randomisation with a block size of four. This will be performed by an independent researcher. Group allocation will only be revealed to participants following the collection of baseline data.

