### Sample size calculation

The calculation is based on the primary research question. Power analysis using GPower 3.1.2 has indicated that 484 participants will provide 95% power to detect a small to medium effect of 0.3 [21] where α = 0.05. The effect size of 0.3 is based on a recent meta-analysis examining the effectiveness of interventions in changing risk appraisals, intentions and behaviour [22]. Due to the tendency for individuals within a cluster to be more similar to each other than those in other clusters, it is necessary to make adjustments to avoid an overestimation of power [23]. In order to obtain this adjusted sample size, the sample size determined by usual procedures is inflated by multiplication with a factor. This factor is known as the “design effect” and is calculated as:

$$1+\left(n–1\right)\mathrm{ICC}$$

where *n* is the average cluster size, and ICC is the intraclass correlation coefficient. The ICC for intention to use condoms between schools is not known but an estimate of 0.01 is reasonably conservative [23]. With ten schools and an average cluster size of 60 (×2 classes of 30 pupils), the design effect is:

$$1+\left(60–1\right)0.01=1.59$$

Accordingly the adjusted sample size is 484 × 1.59 = 770. We will over-recruit to allow for drop-out between the start of the study and the three month follow-up.

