#### To examine the effect of the intervention

Analysis of Covariance (ANCOVA) will be performed to examine differences in condom use intentions (at time two and at follow-up), and behaviour. This will control for demographic variables (gender, ethnicity, age), behaviour at time one, and measures of risk appraisal, and coping appraisal.

If the lesson is effective in increasing condom use intentions, mediation analysis [28] will be conducted to identify whether changes in risk appraisals and/or coping appraisals are responsible for this change. This will help to identify the mechanism of change and indicate where future research and/or resources should be focussed.

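### Removing school codes before a plain ANCOVA leaves no means of allowing for clustering; at the plan's own ICC a nominal 5% test has a false-positive rate of about 12%

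*Protocol article*

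**What the plan says.** Under Randomisation and allocation concealment, the protocol article says "we will use cluster randomisation using schools as the randomisation unit". Under Sample size calculation, it notes that pupils in a cluster resemble each other and that "it is necessary to make adjustments to avoid an overestimation of power". It takes an ICC of 0.01 and 60 pupils per school, obtains a design effect of 1.59, and raises 484 pupils to 770.

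Under Statistical analysis it then prescribes a data step: "Prior to analysis, school codes will be removed from the data set by an independent researcher and intervention condition coded as A or B". The purpose follows: "This will blind analysts to intervention condition". The next subsection, on the effect of the intervention, names the model: "Analysis of Covariance (ANCOVA) will be performed to examine differences in condom use intentions (at time two and at follow-up), and behaviour". The covariates are given as: "This will control for demographic variables (gender, ethnicity, age), behaviour at time one, and measures of risk appraisal, and coping appraisal". School is not among them. The article mentions no replacement school identifier, random effect, cluster-robust variance or analysis of school means.

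**The concern.** The design and the sample size recognise that the school is the unit of allocation. The analysis section removes the variable needed to respect that. An ANCOVA on pupils with no school term computes its standard error as if each pupil had been randomised separately, so the standard error is too small whenever schools differ.

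This is more than detail left to an analysis plan. Once the codes are gone from the analysts' data, a random school effect, clustered standard errors and a comparison of school means are all impossible. An analysis plan that specified one of them would contradict this step.

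The p-values and intervals for intention (the primary outcome) and for condom use are both affected. Mediation analysis is to be run only if the lesson appears to raise intentions, so a false positive there carries forward. The Discussion says an effective lesson can be recommended for wide use in schools. Chance differences between about ten schools could produce that result.

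**Working it through.** **Inputs, all from Sample size calculation:** ten schools; m = 60 pupils per school; ICC 0.01; effect size 0.3; power 95%; α = 0.05; unadjusted N = 484; adjusted N = 770.

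**Reproducing the plan's figures**
- Design effect: DE = 1 + (60 − 1) × 0.01 = 1.59.
- Adjusted size: 484 × 1.59 = 769.6, i.e. 770.
- Unadjusted size: a two-sample t-test at d = 0.3 and 95% power needs 242 per arm (484 in all) one-sided, or 290 per arm (580) two-sided. So 484 reproduces only as a one-sided figure. The article does not state the sidedness.

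**False-positive rate when school is ignored**

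The true variance of the arm difference is DE times the variance that the model assumes. The test statistic under the null therefore has standard deviation √DE, and

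actual two-sided α = 2[1 − Φ(1.96/√DE)].

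At DE = 1.59: √1.59 = 1.261; 1.96/1.261 = 1.554; α = 0.120. Coverage of a nominal 95% interval is 1 − 0.120 = 88%.

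| Pupils per school | ICC | DE | Actual two-sided α |
|---|---|---|---|
| 60 | 0.005 (assumed) | 1.295 | 8.5% |
| 60 | 0.01 (plan) | 1.59 | 12.0% |
| 77 | 0.01 (plan) | 1.76 | 14.0% |
| 60 | 0.02 (assumed) | 2.18 | 18.4% |
| 60 | 0.05 (assumed) | 3.95 | 32.4% |

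The row with 77 pupils applies if the 770 come from ten schools (770/10 = 77). At 60 per school, 770 pupils would need 770/60 = 12.8, i.e. 13 schools. The article says the ICC is not known, so values other than 0.01 are assumptions.

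For a one-sided 5% test the rate at DE 1.59 is 1 − Φ(1.645/1.261) = 9.6%.

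**Simulation check**

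In 40,000 null trials with five schools of 60 per arm and ICC 0.01, the analysis that ignores school rejected in 12.0%. A t-test on school means with 8 degrees of freedom rejected in 5.0% of the same trials. A 6 v 4 split of schools also gave 12.0% when school was ignored.

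**Why the larger N does not help**

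Actual α depends on DE, which is set by cluster size and ICC. Total N does not enter the formula. Inflating N protects power for an analysis that allows for clustering, but it leaves a naive standard error too small by the factor √DE.

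**The case against.** **Removal may be loose wording for blinding.** The article does not say the codes are destroyed, and the exclusion of whole classes or schools that drop out needs membership at some stage. That is fair. But the exclusion can be made before the codes are taken out, and no replacement identifier is mentioned. In one sentence the arm is recoded while the school codes are removed. A data manager following it literally would hand over a file without clusters, so the wording needs correcting even on the milder reading.

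**The text does not call the ANCOVA pupil-level, and a cluster term could sit in the analysis plan.** The first half is true: this is an inference. Individual covariates and no school code leave no other workable reading. If the missing cluster term stood alone, it would be a weak point; the removal of the codes is what settles it.

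**The 12% is conditional.** This stands. It assumes the covariates explain none of the between-school variance. If they reduce the ICC to 0.005 the rate is 8.5%, and at 0.0025 (DE = 1.1475) it is 6.7%. The plan holds that "an estimate of 0.01 is reasonably conservative", so on its own view the ICC is unlikely to be higher, and the 18% and 32% figures rest on assumed values.

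**Behaviour is less affected.** This also stands. The behaviour hypothesis concerns sexually experienced pupils, whom the article expects to be a limited share. Assuming 15 per school at ICC 0.01, DE = 1.14 and the rate is 6.6%. No figure is available for mediation.

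These points change the size. In every case with a positive ICC the error rate stays above nominal.

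**Conclusion.** The concern holds. As written, the plan rules out an analysis that respects the unit of randomisation. At its own ICC and cluster size, the primary two-sided test has a true error rate of about 12%, more than twice the nominal 5%; with 77 pupils per school it is 14%. This rests on a pupil-level ANCOVA, equal school sizes, and covariates that leave the ICC at 0.01. If covariates absorb part of the school variation, a range of about 7% to 12% is reasonable for the primary outcome at 60 per school. It is higher if the true ICC exceeds 0.01. The primary test is not valid as described, and this must be fixed before the data set is prepared.

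**What to change.** **Statistical analysis section.** Say that school and class codes will be replaced by meaningless identifiers, that the independent researcher holds the key, and that the arm is coded A or B. This serves the stated blinding purpose and keeps the clusters in the data.

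**Section on the effect of the intervention.** Replace the plain ANCOVA with one of these:
- a linear mixed model with a random intercept for school and a small-sample degrees-of-freedom correction (Kenward-Roger or Satterthwaite; about 8 for ten schools); or
- a school-level analysis, for example adjusting for pupil covariates first and then comparing school mean residuals by t-test.

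Apply the same allowance for clustering to behaviour and to mediation. A class-within-school term is optional: with two classes per school it would be poorly estimated, and the school term is what the randomisation requires.

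**Cost.** Two changes of wording and no new data. Intervals become wider, as they should. A valid analysis will also show the design's actual power. With five schools per arm, d = 0.3, ICC 0.01, 8 degrees of freedom and no gain from covariates, the standard error is √(2 × DE/(5m)).
- m = 77: √(2 × 1.76/385) = 0.0956, non-centrality 0.3/0.0956 = 3.14, two-sided power about 78%.
- m = 60: √(2 × 1.59/300) = 0.1030, non-centrality 2.91, power about 72%.

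The shortfall from the planned 95% belongs to the design and is not caused by the fix. The sponsor should know of it when deciding how many schools to recruit.

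### Missing outcomes are filled with an unspecified mean: arm means would make the standard error too small, and the overall mean would dilute the effect

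*Protocol article*

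**What the plan says.** The Statistical analysis section opens its missing-data rule with the intention-to-treat principle: "Intention to treat analysis will be used so that data is used regardless of whether pupils are present or absent" at the lessons. The same sentence goes on to say that "means are imputed for pupils with missing post-delivery and/or follow-up data". No type of mean is named, and the article mentions no variance correction, multiple imputation or sensitivity analysis.

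The rule covers the primary outcome, given under Primary outcome as "Intention to use condoms during vaginal sex with casual sexual partners over the next two months". The section on examining the effect of the intervention then states: "Analysis of Covariance (ANCOVA) will be performed to examine differences in condom use intentions (at time two and at follow-up), and behaviour".

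Loss is expected. The Sample size calculation says "We will over-recruit to allow for drop-out between the start of the study and the three month follow-up", but gives no rate.

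**The concern.** Filling a gap with a single mean treats an invented value as a measured one. The effect on the result depends on which mean is meant.

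- **Mean of the pupil's own arm.** The estimated difference does not move, but the spread is understated and the number of pupils overstated. The standard error is too small and the test rejects too often.
- **Mean of both arms together.** Every filled pupil contributes no difference between arms, so the estimate is pulled toward zero.

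Neither version uses the pupil's own baseline answers. Because the text does not choose between them, the same data could give an overconfident result or a diluted one. The primary comparison is affected, and the Discussion would use an effective result to recommend the lesson for wide use in schools.

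The wording also places the imputation under intention to treat. Keeping pupils in their allocated arm whatever their attendance is intention to treat. Assuming that an absent pupil would have scored a mean is a different matter and needs its own justification.

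**Working it through.** **Inputs.** From the Sample size calculation: "484 participants will provide 95% power to detect a small to medium effect of 0.3", α = 0.05, average cluster size 60 and ICC 0.01. Assumed, because the article gives no figure: a share p missing of 5% to 30%, equal in both arms, missing at random, with independent pupils and SD 1.

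**The plan's own figure.** A one-sided t test at 0.05 with 95% power and effect 0.3 needs 242 per arm, 484 in total. A two-sided test would need 580, so 484 reproduces only as one-sided, which the text does not say. The design effect is 1 + 59 × 0.01 = 1.59, and 484 × 1.59 = 769.6, or 770. I use 242 per arm as the base.

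**Arm-mean filling.** With n pupils per arm, n(1 − p) are observed.
- True SE of the difference: √(2 / [n(1 − p)]).
- Filling adds no squared deviations but raises the count to n, so the apparent variance is about (1 − p) and the reported SE is √(2(1 − p) / n).
- Ratio of reported to true SE: 1 − p.
- Actual two-sided error rate: 2 × [1 − Φ(1.96(1 − p))].

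Example at p = 0.20: true SE √(2 / 193.6) = 0.102; reported SE √(1.6 / 242) = 0.081; ratio 0.80.

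**Overall-mean filling.** With equal loss, each arm mean moves a fraction p of the way to the common mean, so the expected difference is (1 − p) × 0.30. The sampling SD of that difference is (1 − p) × √(2 / [n(1 − p)]) = √(2(1 − p) / n), which equals the reported SE. The error rate therefore stays near 5%.

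| Share missing (assumed) | SE ratio, arm mean | Two-sided 5% becomes, arm mean | One-sided 5% becomes, arm mean | Effect 0.30 becomes, overall mean |
|---|---|---|---|---|
| 5% | 0.95 | 6.3% | 5.9% | 0.285 |
| 10% | 0.90 | 7.8% | 6.9% | 0.27 |
| 20% | 0.80 | 11.7% | 9.4% | 0.24 |
| 30% | 0.70 | 17.0% | 12.5% | 0.21 |

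**Simulation** (242 per arm, independent pupils, 8,000 runs per setting, two-sided 0.05), at 10%, 20% and 30% missing:
- Arm mean: error rate 7.7%, 12.1% and 17.6%.
- Overall mean: effect 0.271, 0.242 and 0.208; error rate 4.6%, 4.9% and 4.9%; power 0.88, 0.84 and 0.78.
- Observed values only: effect 0.30 throughout; error rate 5.3%, 5.1% and 5.0%; power 0.88, 0.85 and 0.79.

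**Does covariate adjustment rescue it?** A second simulation used 600 pupils, no clustering and a covariate correlated 0.6 with the outcome (assumed). With ANCOVA, arm-mean filling gave error rates of 7.5%, 12.6% and 17.4% at 10%, 20% and 30% missing, against 5.6%, 5.5% and 5.1% for observed values only. Overall-mean filling again gave 0.27, 0.24 and 0.21. Adjustment does not repair the problem.

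**The case against.** The best defence is that the harm is conditional. The type of mean is a detail that an unseen analysis plan could settle, and the missing rate is unknown. Post-delivery measures are taken immediately after the lessons, so loss there may be small; at 5% missing, the error rate is 6.3% or the effect is 0.285. Under overall-mean filling the test is essentially sound, with power close to that of the observed-data analysis. All of this stands as a limit on size. It does not remove the point, because mean imputation is itself the stated rule, and naming the mean only selects which harm applies. If a pupil's own baseline value were meant, which the text does not say, that would also dilute the effect.

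Four stronger readings are tempting but not supported:

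- **That p-values are wrong whichever mean is used.** This holds for arm-mean filling only (school or class means would act similarly). With the overall mean, the harm is a shrunken estimate.
- **That classes or schools with usable follow-up data are thrown away.** The removal rule covers whole classes or schools that drop out during the study and "don’t provide at least post-delivery data will be removed from the analysis". Both conditions apply, and a class that returns follow-up data has not plainly dropped out.
- **That most loss occurs at follow-up.** This is a fair expectation, but the article gives no figure for either time point.
- **That the error should be quoted jointly with unmodelled clustering.** Treating pupils as independent with a design effect of 1.59 already gives 2 × [1 − Φ(1.96 / √1.59)] = 12.0% with nothing missing. That is a separate issue, and a combined figure would credit imputation with error it does not cause.

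**Conclusion.** The point holds for single mean imputation with the mean unspecified. At assumed losses of 5% to 30%, arm-mean filling raises a nominal two-sided 5% error rate to between 6.3% and 17.0%; overall-mean filling reduces an effect of 0.30 to between 0.285 and 0.21. These are alternatives, not joint effects.

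The figures rest on independent pupils, equal loss in both arms and data missing at random. The size depends on the actual loss, which the article does not project; the direction under each reading does not. The intention-to-treat part is one of labelling: the principle is correctly applied to attendance, and the imputation should not be presented as part of it.

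**What to change.** Delete mean imputation from the Statistical analysis section and replace it with one of two methods:

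1. Analyse all observed post-delivery and follow-up outcomes, as randomised, in a likelihood-based model with baseline intention as a covariate and school accounted for. This is valid under missing at random.
2. Use multilevel multiple imputation, with arm, school, baseline intention and the risk and coping appraisals in the imputation model.

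State intention to treat as analysis by allocated arm regardless of attendance, and give the missing-data assumption in a sentence of its own. A sensitivity analysis for data not missing at random would be useful but is optional.

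Baseline intention and the appraisals are already among the baseline measures, so no new data are needed. The cost is a change of wording and modest programming. Intervals will be wider than under arm-mean filling, because they will reflect the information actually collected.

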Pupils will not be obliged to take part. Quizzes will be administered at the same time as questionnaires at all data collection time points to occupy pupils who do not wish to participate. Pupils will not be required to provide their name (participant responses at each time point will be linked through the demographic information supplied). Pupils will be seated in a manner that prevents classmates from overseeing their responses i.e. in exam conditions. All materials (questionnaires and quizzes) will be placed in a sealed envelope by the individual participants and posted into sealed boxes on completion. Teaching staff will not have access to these. Although parental consent will not be required, as parents of participating pupils will have already consented for their children to participate in SRE and related evaluation activities, a letter outlining the study and their child’s involvement will be sent to all parents through each school as a matter of courtesy. Parents will be given the opportunity to ‘opt-out’ their child at this point.

Baseline measures will be: Demographic information (age, date of birth, gender, and ethnicity), perceived likelihood, perceived severity, response efficacy, self-efficacy, past behaviour, and intention to use condoms during vaginal sex with casual sexual partners for whom STI status is unknown. Provisional measures to be taken at baseline, post-intervention and follow-up are provided in Additional file 1.

After the collection of baseline data, schools will be randomised to receive either the school’s usual teaching on STIs and the chlamydia lesson (intervention arm) or the school’s usual teaching on STIs alone (control arm). This enables the study to evaluate the effectiveness of the chlamydia lesson over and above usual practice. As described above, pupils will be blinded to intervention condition. It is not possible to blind teachers to intervention condition but they will be made aware of the importance of delivering teaching that is consistent with their usual practice. Researchers liaising with schools will offer the same guidance and level of support regardless of intervention condition.

As with all trials of this type, there is the potential for drop-out of whole schools during the study. We have no way of estimating the level of this. Drop-out due to unforeseen circumstances will be planned for and a reserve list of schools will be created to expedite the process of additional recruitment if required.

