### Measures post delivery and at follow-up

Immediately following the lessons, a further set of measures will be taken (see Additional file 1). These will be a repeat of those taken at baseline. For those in the intervention arm, a few additional items will be included to allow for process evaluation. These items will measure participants’ enjoyment of the lesson, collect their opinions on the suitability and relevance of the content for their age, and ascertain the extent to which they felt they could relate to the characters and examples given. It will also determine whether participants felt the materials were engaging, and whether the delivery was sufficiently interactive. Items will be a mixture of fixed response and open-ended formats and will allow any necessary improvements to be made to the lesson following evaluation.

At follow-up, three months post delivery, measures of intention and use of condoms (during vaginal sex with casual sexual partners for whom STI status is unknown) will be taken (see Additional file 1).

A number of the lesson exercises are available as ‘games’ on the HPAs e-Bug website. For this reason, it will be necessary to ensure that those in the intervention group have not viewed these prior to delivery of the lesson, and that those in the control group have not viewed these both before or during the study period. Although we believe this to be unlikely, it will be necessary to determine this to ensure that contamination has not occurred and to control for any dose effect. This will be ascertained using a simple question within the follow-up measure. The reason for not choosing to screen for this at the time of baseline data collection is that doing this may inadvertently draw attention to existence of the ‘games’ and result in participants viewing them out of curiosity resulting in contamination. Data from individuals who viewed the resources prior to delivery of the lesson (intervention group) or before/during study period (control group) will be removed from the analysis.

All questionnaire items will be piloted with approximately five young people prior to use to assess ease of comprehension and the suitability of language. Changes will be made accordingly.

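### The analysis is called intention to treat, yet classes or schools that drop out without post-delivery data are removed after randomisation, even if they could still give follow-up data

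*Protocol article*

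**What the plan says.** The Statistical analysis section of the protocol article names intention to treat and explains it at pupil level: "data is used regardless of whether pupils are present or absent during the STI and chlamydia lessons". It adds that "means are imputed for pupils with missing post-delivery and/or follow-up data". Its next sentence sets a different rule for clusters: "Whole classes or schools who drop-out during the study" and do not "provide at least post-delivery data will be removed from the analysis".

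Three other statements fix how that rule works in practice:

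- Participant recruitment and baseline assessment: "After the collection of baseline data, schools will be randomised to receive either" usual STI teaching plus the chlamydia lesson, or usual STI teaching alone. The same section says that teachers cannot be blinded to their arm.
- Measures post delivery and at follow-up: "Immediately following the lessons, a further set of measures will be taken". Intention and condom use are then measured at follow-up.
- To examine the effect of the intervention: intention is analysed both at time two and at follow-up, and behaviour is analysed as well.

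**The concern.** Intention to treat means that randomised units are analysed in the arm to which they were allocated, whatever happened afterwards. Here a randomised school, or a class within one, can leave the analysis because of something that happens after allocation and that its teachers can influence while knowing the arm.

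The condition for staying in is a measure taken straight after the lessons. Only the intervention arm has an additional lesson to deliver, so withdrawal because that lesson was not taught can arise only there. If such clusters are removed, the comparison moves from all schools offered the lesson towards the schools that taught it, while still carrying the intention-to-treat label.

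The condition also looks at only one of two outcome times. Behaviour after delivery can be measured only at follow-up, and intention is analysed there too. Failing the post-delivery condition is no reason to discard follow-up answers. The article's Discussion says that an effective lesson can be recommended for wide use in schools. For that decision, the effect that counts schools which fail to deliver is the relevant one.

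**Working it through.** **Plan's own figure.** There is none to reproduce. The article accepts that whole schools may drop out and says that it cannot estimate how many.

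**Step 1: order of events.** Baseline, then randomisation, then lessons, then the post-delivery questionnaire, then follow-up. The retention condition is assessed after randomisation, on clusters that already have baseline data.

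**Step 2: how each situation is treated under the stated rules.**

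| Situation | Result under the Statistical analysis section |
|---|---|
| Pupil absent from the lessons | Kept |
| Pupil missing post-delivery and/or follow-up data | Kept, with a mean imputed |
| Cluster does not teach the lesson but returns the second questionnaire | Kept; the removal condition is not met |
| Cluster drops out with no outcome at either time | Removed; there is nothing observed to analyse |
| Cluster drops out before the post-delivery sitting but could answer at follow-up | Removed, on the wording |

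The last row is where the wording itself discards obtainable data. The second row shows that single pupils with the same missing measure are retained.

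**Step 3: can the rule act differently by arm?** Its wording is the same for both. Three facts make a difference possible: the extra lesson exists in one arm only, teachers know the arm, and the post-delivery measure follows the lessons. That a cluster not teaching the lesson will lack post-delivery data is an inference from these facts and is not stated.

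**Step 4: illustration of size.** Inputs:

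- Effect where the lesson is taught: 0.30 SD (the effect size in Sample size calculation).
- Schools: ten (same section). Assumed: five per arm and equal sizes.
- Assumed: *k* intervention schools do not deliver, the effect there is zero, and their outcomes could be collected.

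Effect over all allocated schools = 0.30 × (5 − k)/5. Effect after removal = 0.30, since only delivering schools remain.

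| Not delivering | All allocated | After removal | Ratio |
|---|---|---|---|
| 0 of 5 schools | 0.30 | 0.30 | 1.00 |
| 1 of 10 classes | 0.30 × 9/10 = 0.27 | 0.30 | 0.30/0.27 = 1.11 |
| 1 of 5 schools | 0.30 × 4/5 = 0.24 | 0.30 | 0.30/0.24 = 1.25 |
| 2 of 5 schools | 0.30 × 3/5 = 0.18 | 0.30 | 0.30/0.18 = 1.67 |

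The class row uses two classes per school, as in Sample size calculation.

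If the removed cluster's outcomes cannot be collected at any time, an analysis of the observed outcomes gives about 0.30 whichever rule is written, and the wording makes no difference to the estimate.

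**The case against.** The strongest reply is that the rule has two joint conditions: drop-out, and no post-delivery data. Not teaching the lesson is not the same as dropping out. An intervention school that gives only its usual STI teaching could still hold a sitting after it and be kept. Because post-delivery comes before follow-up, a cluster that has left by then would ordinarily have no outcome at all, and the rule can be read as setting the minimum data for inclusion. Reporting losses by arm and sensitivity analyses may also be set out in an analysis plan that is not shown.

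Much of this stands, and it limits the point. A reader might infer that the rule is a per-protocol exclusion confined to the intervention arm. The text does not support that: it covers both arms, and the link from non-delivery to removal is inferred. A reader might also take 25% as the bias of this trial. It is not, because no rate of non-delivery is given and the figure needs outcomes from the removed school. Nor is lost power a consequence of the wording, since a cluster without outcomes adds no power under any rule. Finally, the reserve list is described only as a means of additional recruitment. The article does not say that reserve schools would take the place of randomised ones in the analysis.

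What the reply does not remove is that the exclusion is stated in the article itself, follows randomisation, depends on conduct by unblinded teachers, and on its wording takes out clusters that could answer at follow-up.

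**Conclusion.** The point holds in a limited form. The Statistical analysis section joins an intention-to-treat label to a post-randomisation exclusion of whole classes or schools, and keys that exclusion to one of the two outcome times. It can differ by arm, but the documents do not show that it will.

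Its size cannot be stated from the article. Under the assumptions in the working, one non-delivering school in five would separate 0.24 SD from 0.30 SD. With no such school, or with no outcomes obtainable from it, the wording would not change the estimate. The change is still worth making, because it settles who is analysed and guards against a bias that could not be repaired once follow-up questionnaires had not been sought.

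**What to change.** Replace the cluster removal sentence with the following rules:

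1. Every randomised class and school with any outcome, post-delivery or follow-up, is analysed in its allocated arm.
2. The second questionnaire is given on a scheduled date, whether or not the lesson was taught, and follow-up questionnaires are still sought from clusters that did not teach it.
3. Only clusters with no outcome at either time are left out. Their number is reported by arm, and a sensitivity analysis assumes no effect in them.

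The cost is a change of wording and some extra contact with non-delivering clusters, for questionnaires that are already planned. The estimate may be somewhat diluted; that is a property of intention to treat and should be accepted as such.
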